##### Aim 3(b):

will fit a series of generalized estimating equations (GEE) models using the SAS® GENMOD procedure with each of the dichotomous adverse events, adherence (21+ sessions or  $\geq 90\%$ ) and satisfaction outcomes as the dependent variable; a binomial distribution for the outcome and a logit canonical link function; intervention arm, delivery model and their interaction as effects of interest; baseline value of outcome and any other measures found to be different between arms or deemed important as additional fixed effects covariates; and an exchangeable working correlation structure to account for clustering due to facility. We will appropriately construct contrasts to test hypotheses of differential proportions with adverse events based on intervention when delivered by staff activity personnel and delivery mode.

#### Aim 4:

We will perform the exploratory analyses to identify combinations of baseline predictors of treatment response and risks of participating in *On the Move* program. We do not anticipate differences in outcomes of *On the Move* program based on delivery mode when a suitable staff person can be trained (Exploratory sustainability Aim 2), and thus propose to combine *On the Move* groups led by exercise leaders and staff activity personnel in the present analysis to maximize sample size and amount of information available for this analysis. In the unlikely event of differences due to delivery mode, we will stratify the Aim 4 analysis by delivery mode.

Adverse events and markers of response to treatment in walking ability have readily available dichotomous operational definitions based on simply presence/absence of an event or evidenced based criteria for having achieved meaningful change in gait speed (0.1+ m/s) and 6MWT (50m).(57) For such dichotomous markers of benefit and harm, we will fit a series of logistic regression models using the SAS® LOGISTIC procedure and classification tree models(67, 68) using Salford Predictive Miner® software with each measure of whether there was a benefit/harm from *On the Move* as the dichotomous response variable; and baseline physical, psychosocial and demographic characteristics as predictors. Logistic regression models are more efficient when associations are linear, and hard-to-discover higher order interactions and non-linearity and/or multicollinearities among predictors do not exist, while classification tree models are more efficient when they do exist. In terms of practically applying prediction criteria, results from logistic regression models require substituting values of predictors to a regression equation while classification tree model produces a flowchart that can be used as is in a clinical setting when a new individual is presented with known predictors. Thus we will use both methods to obtain areas under the receiver operator characteristic curve (AUROCC) to quantify predictive accuracy, and use the results from the method with a greater AUROCC. If the AUROCCs are not substantially different, we will favor the classification tree results due to ease of interpretation and utility in the clinical setting (see **Figure 2** for a hypothetical template for summarization of results). For logistic regression modeling, we will include all available baseline information simultaneously in the model as predictors, and use the backward elimination stepwise procedure to guard against model over-fitting to obtain a parsimonious model with a small number of most relevant predictors to facilitate interpretation, communication and clinical utility of the model. For the classification tree models, we will use all predictors available and use a minimum misclassification-complexity cost tree to achieve the same objectives. We will use the method of DeLong(69) to obtain the statistical significance of the improvement in predictive accuracy, as measured by AUROCC.

Our LLFDI function and disability outcomes do not have the same level of evidence based for creating intuitively appealing dichotomous measures of treatment response. Thus we will consider pre- to post-intervention change as a continuous variable, and perform analogous analysis to that for dichotomous outcomes but with appropriate statistical models. Specifically, we will fit standard multiple linear regression models using the SAS® REG procedure and regression tree models(67, 68) using Salford Predictive Miner®; and use proportion of explained variance ( $R^2$ ) to quantify predictive accuracy.

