### 9.2 Sample Size

We base our sample size justification on prior data from our RESTORE and PRIME pilot studies, two-tailed tests conducted at the  $\alpha=0.05$  level, a conservative attrition rate of 10% between baseline and follow-up assessments, practical consideration of a class size of 10 participants for group exercise, computational techniques that match our study design and proposed analytical approach as much as possible within the constraints of already published methodologies and commercially available sample size and power software (PASS 2002®, Number Cruncher Statistical Systems, Inc., Kayesville, Utah), and ability to detect differences that correspond to published meaningful change criteria(57) or moderate Cohen's effect sizes of  $d=0.5$ .(58)

The numbers needed to enroll in order to detect statistical significance of intervention effect when delivered by an exercise leader (Aim 1), are presented in **Table 1**. We take into account the clustering of participants by facility by assuming an intracluster correlation of 0.1 and a resulting design effect of 1.90 to appropriately inflate the sample size accordingly.(59) In

summary, a total of 280 participants with 140 in each arm will allow us to detect statistical significance in intervention effects in all main outcomes with at least 80% statistical power.

**Table 1. Number needed to enroll for detecting effects of intervention incorporating clustered design (x1.90), attrition (10%), and rounded up to class size of 10.**

| Outcome                    | Prior Information                |                                 |                                         | Estimated Sample Size                                   |                                 |
|----------------------------|----------------------------------|---------------------------------|-----------------------------------------|---------------------------------------------------------|---------------------------------|
|                            | Baseline Standard Deviation (SD) | SD in Baseline-Follow up Change | Meaningful Difference Targeted (Source) | Completers Needed Per Arm assuming No Clustering | Number Needed to Enroll Per Arm |
| LLFDI Overall Function     | 6.15                             | 4.86                            | 3.08 ( $d=0.5$ )                        | 41                                                      | 90                              |

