#### Aim 3(a):

We will fit a series of generalized estimating equations (GEE) models using the SAS® GENMOD procedure with each of the dichotomous adverse events, adherence (21+ sessions or  $\geq 90\%$ ) and satisfaction outcomes as the dependent variable; a binomial distribution for the outcome and a logit canonical link function; intervention arm, as the effect of primary interest; baseline value of outcome and any other measures found to be different between arms or deemed important as additional fixed effects covariates; and an exchangeable working correlation structure to account for clustering due to facility. We will appropriately construct contrasts to test hypotheses of differential proportions with adverse events based on intervention when delivered by exercise leaders.

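### Aim 4's logistic, linear and DeLong analyses treat residents of one facility as independent; the effect is small unless a predictor clusters strongly by facility, and the repair needs a small-sample correction

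*Supplement*

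**What the plan says.** In Version 2.0, section 9.3.3, Aim 4 pools the On the Move participants from both delivery modes and looks for baseline predictors of benefit and harm.

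- Dichotomous outcomes (adverse events, meaningful change in gait speed and 6MWT): "For such dichotomous markers of benefit and harm, we will fit a series of logistic regression models using the" SAS LOGISTIC procedure. Everything recorded at baseline is entered and then reduced by backward elimination.
- LLFDI change: "we will fit standard multiple linear regression models using the" SAS REG procedure.
- DeLong's method is used "to obtain the statistical significance of the improvement in predictive accuracy, as measured by AUROCC".
- Classification and regression trees are fitted alongside.

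The Aim 4 text names no facility term, GEE, robust variance or facility-level resampling, and the sensitivity analyses in 9.3.4 add none.

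Elsewhere the plan does allow for facility. Section 9.2 says: "We take into account the clustering of participants by facility by assuming an intracluster correlation of 0.1". Aims 1 and 2 include a facility random effect. Aims 3(a) and 3(b) use GEE with "an exchangeable working correlation structure to account for clustering due to facility".

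**The concern.** Facilities are the randomised unit and classes run within them, so outcomes of residents in one building may be correlated. If a baseline characteristic also differs between buildings, an ordinary regression slope has a standard error that is too small, and elimination based on p-values keeps the characteristic too often. The DeLong variance has the same weakness.

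This is a stated choice of method, not a detail left open. It also means that adverse events are tested with clustering in Aim 3 and without it in Aim 4. Aim 4 is meant to inform residents' decisions about joining the programme. A characteristic that mainly marks which building a person lives in could therefore enter the reported prediction rule.

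**Working it through.** **The plan's own figure.** Section 9.2 uses a class size of 10 and states "assuming an intracluster correlation of 0.1 and a resulting design effect of 1.90". Check: 1 + (10 − 1) × 0.1 = 1.90. Table 1 follows with a two-sample t-test at two-sided 0.05 and 80% power. Completers of 41, 37, 64 and 13 per arm, multiplied by 1.90/0.90, give 86.6, 78.1, 135.1 and 27.4, which round up to 90, 80, 140 and 30. The plan gives no comparable calculation for Aim 4.

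**Inputs for Aim 4.**
- Facilities: about 34 sites (section 4), allocated 1:1, so 17 in On the Move.
- Participants: 140 + 60 = 200 (Table 4 heading). With 10% attrition, 200 × 0.90 = 180 completers, so m = 180/17 = 10.6 per facility.
- Outcome ICC: 0.1, the design assumption of section 9.2.
- Predictor ICC: not in the documents, so a range is shown.
- Elimination threshold: not in the documents; 5% two-sided is assumed.

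**Formulas.** Variance inflation of an ordinary regression slope: DE = 1 + (m − 1) × ICC_outcome × ICC_predictor. Actual error of a nominal 5% test: 2 × [1 − Φ(1.96/√DE)]. At predictor ICC 0.3, for example, DE = 1 + 9.6 × 0.1 × 0.3 = 1.29, 1.96/√1.29 = 1.73, and the error is 8.4%.

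Error rates per null predictor, by formula and by simulation with 17 facilities and 180 completers:

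| Predictor ICC | DE | Formula | Linear, two simulations | Logistic, latent ICC 0.1, 35% responders | Logistic, outcome ICC about 0.1 | DeLong, two null markers |
|---|---|---|---|---|---|---|
| 0.1 | 1.10 | 6.1% | 6.5%, 6.3% | 6.8% | 5.5% | 6.3% |
| 0.3 | 1.29 | 8.4% | 8.1%, 8.3% | 7.1% | 7.7% | 9.1% |
| 0.5 | 1.48 | 10.7% | 11.1%, 9.9% | 7.9% | 11.5% | not run |
| 1 (constant within facility) | 1.96 | 16.1% | 16.4%, 16.4% | 11.5% | 17.1% | 17.1% |

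At predictor ICC 0 the second linear simulation, the second logistic one and DeLong gave 4.5%, 5.1% and 5.3%. The two logistic columns differ, possibly because the first sets the ICC on the latent scale. A further simulation of the same set-up gave 5–10% over predictor ICCs of 0.1 to 0.5. Allowing for that and for simulation error, I take about 5–6% at predictor ICC 0.1, 5.5–8% at 0.3 and 7.5–11% at 0.5 for the regression models.

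**Sensitivity to the outcome ICC** (formula, all 200 enrolled, m = 11.8; predictor ICC 0.1, 0.3, 0.5 and 1 in turn):
- Outcome ICC 0.1: 6.3%, 8.8%, 11.4%, 17.4%.
- Outcome ICC 0.05: 5.6%, 6.9%, 8.2%, 11.4%.
- Outcome ICC 0.02: 5.2%, 5.7%, 6.3%, 7.5%.

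**Does a facility-adjusted model repair it?** Simulated with 17 facilities and 180 completers:
- GEE with the default sandwich variance, one predictor, 1,200 runs: 8.3%, 7.8% and 11.5% at predictor ICC 0.1, 0.3 and 1, against 5.3%, 6.7% and 11.5% for ordinary logistic regression. A second simulation of default GEE gave 7–8% at 0.1–0.5 and 12.6% for a facility-constant predictor.
- Default GEE with fifteen predictors, 200 runs: 9.0% and 11.8% at 0.1 and 0.3, against 6.2% and 7.4% for ordinary logistic regression.
- Facility random effect fitted by REML: 4–6%.
- GEE with a bias-reduced variance and t reference: 4–5%.

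**The case against.** The strongest reply is that the effect is minor for the analysis as written. Aim 4 describes its predictors as physical, psychosocial and demographic characteristics of participants. Facility type is not listed, and the documents give no predictor ICC. A reader might infer from the bottom row of the table that null predictors are typically kept 12–17% of the time. The documents do not support that: those rates need a variable that is constant within a facility. This part of the reply stands.

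Other points also stand:

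- The 0.1 is a sample-size assumption for the continuous main outcomes, not an estimate for responder status or adverse events.
- If the AUROCCs are similar, the plan favours the tree, which is pruned on misclassification cost and complexity. The p-value mechanism does not reach it.
- A reader might expect the plan to report predictor confidence intervals that are too narrow, but Aim 4 promises none. Its accuracy measures are AUROCC and R-squared.
- Major adverse events are expected in under 1% of people, fewer than 2 of 180, so no multi-predictor model is informative for them.
- Copying the Aim 3 GEE into Aim 4 with default settings would not mend the problem and could make it worse.

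The exploratory label does not answer the point. It excuses Aim 4 from multiplicity control but does not make an independence assumption true. Aims 2 and 3(b) sit in the same exploratory section and still model facility.

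**Conclusion.** The point holds as a minor improvement. Aim 4 names LOGISTIC with backward elimination, REG and DeLong comparisons, all of which ignore facility, in a plan that allows for facility everywhere else. Under the inputs above, the excess over a nominal 5% is negligible for predictors that barely cluster and at most about 1 point at predictor ICC 0.1. It is up to about 3 points at 0.3, and about 2.5 to 6 points at 0.5. The 12–17% range is an upper bound for the case where something like facility type is entered.

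A smaller outcome ICC shrinks all of these figures; fewer facilities enlarge them. With 14 facilities and 200 participants, the facility-constant rate by formula is 19.9%. No confirmatory test, sample size or treatment comparison is affected.

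**What to change.** In section 9.3.3, Aim 4:

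1. For LLFDI change, replace REG with MIXED and a facility random effect.
2. For dichotomous outcomes, replace LOGISTIC with a facility random-effect logistic model, or with GEE using a bias-corrected small-sample variance and a t reference. State that the default sandwich variance will not be used. The simulated support above is for the REML random effect and the corrected GEE; I have no separate figure for a random-effect logistic model.
3. Run backward elimination on those p-values and state the threshold.
4. Obtain the uncertainty of AUROCC and R-squared, and the logistic-versus-tree comparison, by resampling whole facilities instead of using the independent-participant DeLong variance.

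The cost is a few lines of text and code, with no new data. Intervals will be somewhat wider and fewer predictors may be retained.

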### **1.2 Secondary Objectives**

**Aim 2: When feasible to be delivered by staff activity personnel, explore the effectiveness of *On the Move* compared to a standard program; and sustainability compared to delivery by exercise leaders (when feasible). Explore barriers to identifying and training staff activity personnel.** *On the Move delivered by staff activity personnel (when feasible) will produce gains in above outcomes that are greater than the standard program; and comparable to when delivered by an exercise leader.*

**Aim 3: Explore the acceptability and the risks of the *On the Move* and standard exercise programs delivered by (a) exercise leaders and (b) staff activity personnel (when feasible).** *On the Move will result in greater satisfaction and higher attendance rates than the standard program. Attendance rates and satisfaction will be similar for exercise leader and staff activity personnel led programs when feasible to recruit staff personnel. Adverse event (falls, soft tissue injuries, muscle soreness, etc.) rates during exercise will be similar between the two groups and the two facilitators when feasible to recruit staff personnel.*

**Aim 4: Explore potential baseline predictors of benefit and risks of participation in *On the Move* program to facilitate informed patient decision making.** *We will be able to identify combinations of baseline physical, psychosocial and demographic factors associated with each of the treatment response and adverse events outcomes.*

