In the RESTORE study, 50 subjects (mean age 77.2±5.5 years, 65% women) were randomly assigned to either a standard exercise program (endurance, strength and typical static balance training) or a timing and coordination program, for one hour, 2 times per week for 12 weeks, with baseline and 12 week follow up assessments. Of the 50 who entered, 47 (94%) completed the study. Both groups increased gait speed (timing and coordination by 0.21 m/s and standard by 0.14 m/s). The timing and coordination group reduced the energy cost of walking  $0.10 \pm 0.03 \text{ mL/kg/m}$  more than the standard group ( $p=0.0002$ ), had a  $9.8 \pm 3.5$  point greater gain in reported walking confidence (i.e. Gait Efficacy Scale) than the standard group ( $p=0.008$ ), had a  $1.5 \pm 0.6$  point greater reduction in gait abnormalities (i.e. GARSIM) than the standard group ( $p=0.02$ ), and had a  $3.5 \pm 1.7$  ( $p=0.04$ ) point greater gain than the standard group in basic lower extremity function (LLFDI) and a  $2.6 \pm 1.7$  ( $p=0.12$ ) point greater gain than the standard group in advanced LE function (LLFDI).(23)

In the PRIME study, 38 subjects (mean age 78.5±5.6 years, 65% women) were randomly assigned to either a standard endurance and strength exercise program or a timing and

coordination plus strengthening program, 2 times per week for 12 weeks, with assessments at baseline and immediately following the 12 week intervention. Preliminary analyses indicate that the timing and coordination group had greater improvements in gait speed, figure of 8 walk, and challenging gait tasks than the standard group. Both groups had improvements in the 6MWT ( $p<0.05$ ); however, the timing and coordination group had marginally greater improvements ( $p=0.14$ ). Only the timing and coordination group demonstrated improvement in self-reported disability and neither group decreased perceived walking difficulty (LLFDI – total function). However, this group had very high initial LLFDI function scores; reflecting low levels of baseline perceived walking difficulty, so may have been vulnerable to ceiling effects. Since our proposed sample will be more impaired, we anticipate that there is more room for change and that treatment group differences or declines of perceived walking difficulty will be detectable.

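### Aim 4 models outcome in On the Move participants only, so it cannot show who gains from On the Move rather than from the Standard class

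*Supplement*

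**What the plan says.** Section 1.2 of Protocol Version 2.0 sets Aim 4 as the search for baseline predictors of benefit and risk from taking part in On the Move, "to facilitate informed patient decision making".

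Section 9.3.3 (Aim 4) gives the method:

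- **Population.** It pools the On the Move "groups led by exercise leaders and staff activity personnel in the present analysis to maximize sample size". The only split foreseen is that, should delivery mode matter, "we will stratify the Aim 4 analysis by delivery mode".
- **Outcome.** For walking, a participant's own gain of at least 0.1 m/s in gait speed or 50 m in the 6MWT. For harm, presence or absence of an event. LLFDI change is kept continuous and treated in the same way.
- **Models.** Logistic regression and classification trees, "with each measure of whether there was a benefit/harm from *On the Move* as the dichotomous response variable", with "baseline physical, psychosocial and demographic characteristics as predictors".
- **Use.** The section presents the tree as a flowchart that a clinician could apply directly to a new person.

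No Standard participant, arm term or arm-by-predictor term appears. The wait-list comparison in Section 9.3.2 is a sensitivity analysis for Aim 1 only. Section 2 reports that in the RESTORE pilot both groups gained gait speed: "timing and coordination by 0.21 m/s and standard by 0.14 m/s".

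**The concern.** A gain from before to after the class is not the same thing as a gain caused by On the Move. It also contains whatever any exercise class would bring, retest learning, regression to the mean and natural change. Section 9.3.3 (Aim 2) itself allows that people waiting 12 weeks without a class may change.

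A model fitted in one arm cannot tell a factor that goes with improvement in either class from one that enlarges the advantage of On the Move. Regression to the mean makes this concrete. The results template in Section 9.3.4 lists gait speed among the predictors of response. If response is change in gait speed, the baseline value is part of the outcome and can look predictive for that reason alone. Only a comparison arm would expose this.

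The harm side has the same difficulty. Section 1.2 (Aim 3) expects similar event rates in the two programs. If so, an event during On the Move is not an excess due to it.

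At stake is the reading of the flowchart. Residents could be steered towards or away from the program on factors that have no bearing on its advantage over Standard.

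**Working it through.** **Inputs.** SD of gait-speed change 0.20 m/s and target difference 0.10 m/s (Section 9.2, Table 1). Pilot mean gains 0.21 and 0.14 m/s (Section 2). Response threshold 0.1 m/s (Section 9.3.3). Anticipated numbers 140+140+60+60 (Table 4), so about 140 + 60 = 200 per program and, with 10% attrition, 180 completers. Normal change scores are assumed.

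**1. The plan's own figure.** Version 2.0 gives no sample size or performance figure for Aim 4. The nearest figure on the same inputs is the gait-speed row of Table 1. A two-sample t-test with difference 0.10, SD 0.20, two-sided 0.05 and 80% power needs 64 completers per arm (63 by the normal approximation). Then 64 × 1.90 / 0.90 = 135.1, rounded up to 140. Both figures reproduce, so 0.20 is the SD of change that the plan works with.

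**2. Responder shares at the pilot means.** Share = Φ((mean gain − 0.10) / SD).

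| Mean gain (m/s) | Calculation | Share |
|---|---|---|
| 0.21 | Φ(0.55) | 71% |
| 0.14 | Φ(0.20) | 58% |
| 0 | Φ(−0.50) | 31% |

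The matched share is 0.579 / 0.709 = 82%. For an assumed SD of 0.10 to 0.25 it runs from 76% (66% against 86%) to 84% (56% against 67%).

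**3. Responder shares at the trial's target difference.** With SD 0.20 and the Standard gain assumed:

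- Standard gain 0, On the Move 0.10: 30.9% against 50.0%; 0.309 / 0.500 = 62% matched.
- Standard gain 0.14, On the Move 0.24: 57.9% against Φ(0.70) = 75.8%; 0.579 / 0.758 = 76% matched.

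**4. Effect on the search for predictors.** Simulation with 4,000 runs, 180 completers per arm, pilot means, SD 0.20, a binary 50/50 baseline factor, log odds ratios tested at 1.96, and clustering ignored:

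| Factor | Flagged, On the Move only | Flagged, arm-by-factor test |
|---|---|---|
| Shifts change by 0.10 m/s equally in both arms | 71% | 5% |
| Adds 0.07 m/s under On the Move, offset by −0.07 m/s in both arms | 5% | 24% |

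The one-arm analysis can promote a factor that does not modify the effect and miss one that does.

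**5. What an interaction analysis could detect.** On continuous change with four cells of 90, SE = 0.20 × √(4/90) = 0.0422. Power = Φ(difference / SE − 1.96):

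- 0.05 m/s: 22%
- 0.07 m/s: 38%
- 0.10 m/s: 66%

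**6. Adverse events.** Section 7.1 expects falls and cardiac events in under 1% of people and minor events in 1% to 10%. With about 200 per program, that is fewer than 2 people, and about 2 to 20 people. Arm-by-predictor logistic models are not workable at those counts.

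**The case against.** The strongest reply is that Aim 4, unlike the other aims, names no comparator. Its hypothesis is only that baseline factors will be associated with response and with events, and the planned models deliver that. Relative effect is the business of Aims 1 to 3. A resident deciding whether to join an On the Move class can sensibly use the expected outcome and the absolute risk in that class. The aim is also secondary and exploratory. All of this stands, and it is why the one-arm model should be kept. It does not justify calling the outcome benefit or harm from On the Move, or offering the result as a clinical flowchart under that name.

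Three stronger readings are tempting, and the documents do not support them:

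- **That the model finds who improves in any class.** It finds who improves, or has an event, under On the Move. Prognosis and true effect modification are mixed there and cannot be separated.
- **That some four fifths of the response in this trial is shared with Standard.** The 82% rests on RESTORE: slower walkers with variable gait, one-on-one delivery, and a comparator of endurance, strength and balance training. This trial's Standard class is mostly seated.
- **That interaction models should be fitted throughout.** Power is low, and the plan already enters all baseline variables at once, so an interaction for each would double the terms. For adverse events the counts rule it out.

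**Conclusion.** The concern holds in this form: as planned, Aim 4 predicts outcome among On the Move participants and cannot show who gains from On the Move rather than Standard. No other section of Version 2.0 supplies the missing comparison.

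On the trial's own target difference, about 62% to 76% of the gait-speed response rate in On the Move would be matched under Standard. This assumes normal change, SD 0.20 m/s and a Standard gain between 0 and 0.14 m/s. It compares rates and does not say which individuals would have responded anyway. The pilot-based 71% against 58% is illustrative only, and the simulation shows what a prognostic factor would do, not that such factors dominate here.

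The primary analysis is untouched and the exploratory label lowers the weight of the point. It does not remove it, because a larger sample would not separate prognosis from treatment-specific benefit within one arm.

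**What to change.** Revise Section 9.3.3 (Aim 4) as follows:

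- Keep the On the Move-only models, but describe them as predicting improvement or events during On the Move.
- Apply the resulting tree nodes or risk groups to the Standard arm. Report response and adverse event rates in each arm, and the between-arm difference.
- For the walking and LLFDI outcomes, add arm and arm-by-predictor terms for the retained predictors, allowing for facility clustering.
- Call a factor a predictor of benefit from On the Move only if the between-arm difference varies with it.
- For rare adverse events, give descriptive rates by arm and no interaction models.

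The cost is wording and some programming; both arms already provide the measures (Sections 6.1 and 6.2.3). The downside is imprecision: about 38% power for a 0.07 m/s interaction and 66% for 0.10 m/s, before clustering. Few factors will stand out, and a modifier dropped when predictors are selected in On the Move alone will not be tested. The results should therefore stay labelled exploratory.

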#### 9.3.4 Additional

Exploratory/Sensitivity  
and  
Compliance/Dropout  
Analyses

**Figure 2.** Hypothetical template for summarization of Aim 4 results.

Figure 1. Predictors of treatment response using age, gait speed, and fear of falling. Area under ROC curve=0.797

[figure not shown]

We will perform additional analyses to extend our findings, generate new hypotheses, assess robustness and potentially refine conclusions. They will include using an alternative threshold besides 90% to operationally define high level of adherence/compliance calculating proportion missing each session to describe the pattern of adherence/compliance over time; assessing intervention effects using as-treated instead of intention-to-treat philosophy; and alternative operational definitions of treatment response such as combinations of walking ability, function and/or disability, and reaching a published threshold such as 0.4(0.8) m/s in gait speed for limited(full) community ambulation.(70)

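### Aim 4 selects its prediction model and reports its accuracy by an AUROCC (R-squared for LLFDI) with no validation or optimism correction described

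*Supplement*

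**What the plan says.** The rule is in Section 9.3.3, Aim 4, of protocol Version 2.0. On the Move participants from both delivery modes are pooled. For adverse events and for meaningful change in gait speed or 6MWT, a logistic model and a classification tree are each built from all available baseline variables.

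The AUROCC from each method is the measure of predictive accuracy, and the plan will "use the results from the method with a greater AUROCC". There is also a tie rule: "If the AUROCCs are not substantially different, we will favor the classification tree results due to ease of interpretation". No threshold for a substantial difference is given. The DeLong method supplies the significance of any gain in AUROCC.

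Two safeguards are named. On the logistic side the plan will "use the backward elimination stepwise procedure to guard against model over-fitting"; on the tree side it will "use a minimum misclassification-complexity cost tree to achieve the same objectives".

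For LLFDI function and disability the plan will "perform analogous analysis to that for dichotomous outcomes but with appropriate statistical models", that is, linear regression and regression trees judged by R-squared.

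One reason given for preferring the tree is that it "produces a flowchart that can be used as is in a clinical setting". Section 1.2 gives the purpose of Aim 4 as helping patients make informed decisions.

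**The concern.** One statistic does two jobs: it picks the winning method and it is then published as that method's accuracy. Backward elimination and cost-complexity pruning limit the size of a model. They do not remove the optimism in an AUROCC computed on the same data that chose the variables, the splits and the pruning level. Taking the larger of two such values adds a little more. The two methods also need not be equally optimistic, so the comparison between them can be uneven.

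The DeLong test compares AUROCCs from given sets of predictions. Applied to fitted-data predictions, it would test a difference that includes each model's own optimism.

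What is at stake is the accuracy figure attached to a flowchart or equation meant to inform patients. That use depends on performance in new people, which an apparent AUROCC does not measure.

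**Working it through.** **No plan figure to reproduce.** The documents state no expected accuracy for Aim 4. The template for Figure 2 in Section 9.3.4 carries "Area under ROC curve=0.797", but it is labelled hypothetical and is not a result or a target.

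**Inputs from the documents**
- Arm sizes: Table 4 anticipates 140 + 60 = 200 On the Move participants. The 140 follows from gait speed in Table 1: 64 × 1.90 / 0.9 = 135.1, rounded up to 140.
- Attrition: 10% (Section 9.2), so 200 × 0.9 = 180 completers.
- Less severe adverse events: 1–10% of people (Section 7.1). One scenario uses 7%, or 0.07 × 180 = 12.6 events.

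**Assumptions, because the plan is silent**
- 12, 15, 20, 25 or 30 candidate predictors.
- 25%, 40% or 50% responders.
- Stay level 0.05 or 0.10.
- Tie tolerance 0 to 0.05.
- Tree grown with equal or data priors and sized by 10-fold cross-validated minimum cost (0-SE) or the 1-SE rule, or else fixed at 4 to 8 leaves.

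**Method.** Predictors were generated independently of the outcome, so the true AUROCC is 0.50. Both models were fitted and both AUROCCs computed on the fitting data. The larger was reported, with the tree favoured within the tolerance. There were 130 replicates per scenario (100 for fixed-size trees). True performance was measured on 2000 fresh cases.

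**Results.** n = 180, 20 predictors and stay level 0.05 unless stated. The range for the tree being picked runs from tolerance 0 to 0.05 and counts only trees with at least one split.

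| Tree setting | Scenario | Tree picked | Reported AUROCC, mean (median) |
|---|---|---|---|
| 0-SE, equal priors | 40% response | 72–80% | 0.77 (0.79) |
| 0-SE, equal priors | 40%, stay level 0.10 | 66–75% | 0.77 (0.77) |
| 0-SE, equal priors | 50% response | 58–65% | 0.72 (0.68) |
| 0-SE, equal priors | 25% response | 61–66% | 0.74 (0.71) |
| 0-SE, equal priors | 40%, 12 predictors | 72–77% | 0.74 (0.70) |
| 0-SE, equal priors | 40%, 30 predictors, n = 200 | 60–69% | 0.75 (0.69) |
| 0-SE, equal priors | 7% event rate | 68–74% | 0.81 (0.83) |
| 0-SE, data priors | 40% response | 15–21% | 0.61 (0.60) |
| 0-SE, data priors | 25% response | 5–7% | 0.59 (0.61) |
| 1-SE, equal priors | 40% response | 37–42% | 0.64 (0.62) |
| Fixed 4 leaves | 40%, 15 or 25 predictors | 95–100% | 0.69–0.70 |
| Fixed 5 leaves | same | 95–100% | 0.72–0.74 |
| Fixed 6 leaves | same | 95–100% | 0.75–0.77 |
| Fixed 8 leaves | same | 95–100% | 0.80–0.82 |

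The 95–100% range is for the fixed-size trees taken together. Spread within a scenario is wide: the first row has an interquartile range of 0.63 to 0.92. With 130 replicates the standard error of a selection percentage is at most √(0.5 × 0.5 / 130) = 0.044, about 4 points.

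The logistic model's apparent AUROCC averaged 0.55–0.65, so it too is optimistic, though generally less than a tree that has been allowed to grow. On fresh cases both methods averaged 0.499–0.502 throughout. A rule based on properly validated AUROCCs would therefore centre on about 0.50 here.

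No simulation was run for R-squared or for the DeLong test. Those parts rest on the same reasoning: a fit statistic computed on the data used for selection is optimistic.

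**The case against.** The strongest reply is that the plan never says the AUROCC is in-sample. That is correct. A reader might infer that fitting-data evaluation is the stated rule, but the text does not support this; it is silent. The silence is still a gap, because an analyst who used the fitting data would be following the plan as written, and the choice of data decides both the winner and the reported accuracy.

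A reader might also infer that the rule nearly always picks the tree, or that it yields one predictable false value. It does not. Under data priors or a 1-SE rule the tree was picked in only 5–42% of runs, with means of 0.59–0.64. Because the plan fixes none of these settings, only a conditional range is defensible. Nor is the 0.797 in the template evidence of anything: it is a placeholder.

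It is fair to add that over-fitting was considered, since two safeguards are named, and that the remark about clinical use contrasts a flowchart with an equation rather than committing this trial's tree to practice. Aim 4 is also labelled exploratory and nothing in Aims 1 to 3 depends on it. All of this lowers the severity. None of it makes an uncorrected accuracy figure sound.

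**Conclusion.** The point holds in conditional form. Aim 4 chooses its model and reports its accuracy by AUROCC or R-squared with no validation or optimism correction described. If the AUROCC comes from the fitting data, noise alone gives a mean reported value of 0.59 to 0.82 where the truth is 0.50. It was inflated in every setting tried, and the unfixed settings alone move it by about 0.2 (0.82 − 0.59 = 0.23).

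These sizes assume about 180 completers, 12 to 30 predictors, and 25–50% responders or a 7% event rate. If the analysts already intend a validated AUROCC, the defect reduces to missing wording. This should be corrected, but it does not touch the primary analysis.

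**What to change.** In Section 9.3.3, Aim 4:
- Select the method and report its accuracy by cross-validated or bootstrap optimism-corrected AUROCC, and by R-squared corrected in the same way for the LLFDI outcomes. Repeat variable selection, tree growing and pruning inside every resample.
- Do not apply the DeLong test to fitted-data predictions.
- Show apparent values only beside the corrected ones.
- Fix in advance the tree settings (priors, misclassification costs, SE rule, how tree size is chosen), the stay level for backward elimination, and the difference in AUROCC that counts as substantial.

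The cost is some plan wording and a modest amount of code; no new data are needed. The reported accuracy will probably be lower.
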